### Sample size

The sample size calculations were based on assumptions of an average of 40 residents in each care home, and that at least 60 % of these would meet the eligibility criteria and 65 % of those eligible would be willing to provide informed consent (i.e. 15 residents recruited from each care home). Calculations were based on a normally distributed outcome: the mean difference in CMAI scores between arms at 16 months. Fifty care homes, each recruiting 15 residents, will result in 750 residents overall and provide 90 % power to detect a clinically important difference of 3 CMAI points (standard deviation (SD) 7.5 points) with a two-sided 5 % significance level. This allows for 25 % loss to follow-up (cluster size of 11 residents available for analysis) based on Chenoweth et al. [14] leading to an inflation factor of 2.0 (intracluster correlation coefficient (ICC) no greater than 0.1). The assumption that the ICC will be no larger than 0.1 was based on an ICC for CMAI reported by Fossey et al. [27] when evaluating effectiveness of a psychosocial intervention on antipsychotic use in nursing home residents with dementia.

### Methodological improvements building on previous studies

Through correspondence with the authors of all three previous trials on the efficacy of DCM™, we were able to identify key study design strengths, challenges and difficulties encountered. Key methodological developments in the EPIC trial include:Adoption of a pragmatic trial design. This enables generalisation of the treatment effects to practice in the UK and important data to be collected on cost-effectivenessUse of an independent researcher assessment of the primary outcome at each time point, permitting assessment of any bias that may be caused by being unable to blind study participants to intervention allocationCollection of quality of life data from three sources where available – staff-proxy, self-report and relative proxyCollection of quality of life data using three measures, permitting, use of measures we believe to be most sensitive for use in this population (QUALID), quality-adjusted life years (QALYs) to be calculated (DEMQOL-Proxy) and self-report in as many residents as possible (QOL-AD)Randomisation of sites at a care home rather than unit level so there is a significantly reduced chance of control contamination in care home sites where one or more units may be participating but may be randomised to the intervention separatelyInclusion of a process evaluation including in-depth intervention fidelity assessment and qualitative examination of implementation issues

### Statistical analysis

A single final analysis is planned when all follow-up data have been collected and the primary analyses will be carried out on an intention-to-treat basis, utilising all available follow-up data, comparing treatments as allocated.

It is expected that a sizeable proportion of residents will be missing from the main analyses, and that missing data can be predicted by known variables, hence the principal method for handling missing scale data will be multiple imputation under the Missing at Random (MAR) assumption. Sensitivity analyses will be carried out to assess the impact of the choice of imputation model and of assuming data are Missing Not at Random (MNAR) as appropriate.

The impact of cluster randomisation is expected to be equal across arms but that of treatment provision is not. As such, the principal method for handling clustering effects will be to fit a multilevel model that allows care home- and resident-level variances to differ across arms. A sensitivity analysis will be conducted fitting a random intercept model assuming equal total variances. The resident-level primary outcome of agitation (continuous CMAI score) will be analysed at 16 months post randomisation using a linear two-level heteroscedastic regression model [70], adjusting for design factors, with a contrast for intervention and control. The model will be adjusted for the following fixed effects: care home (level 2) covariates (home type and size, provision of dementia awareness training and hub) and resident (level 1) covariates (severity of dementia, age and baseline CMAI score). Unadjusted and adjusted ICCs, treatment effect estimates and corresponding 95 % confidence intervals will be presented.

For residents where a PAS and an abridged CMAI score are also available, a sensitivity analysis will be conducted replacing the CMAI score in the primary analysis with the PAS and abridged CMAI scores looking for consistency in the size and direction of effect.

Secondary outcome measures will be analysed using a similar modelling strategy as described for the primary analysis. Where outcomes are continuous, linear models will be fitted; where binary, logistic models will be fitted. Change in primary and secondary outcomes over time (6 and 16 months) will be analysed with three-level multilevel models with contrasts for treatment, time and the treatment-by-time interaction, in which outcomes are nested within residents and care homes. A similar correlation structure will be assumed for care homes and residents, but correlation over time will also be considered at the outcome level.

A number of exploratory subgroup analyses are planned which will be specified in detail in the Statistical Analysis Plan. These will include care home- and resident-level factors such as type of care home, severity of dementia and NPI subgroup clusters.

### Health economic evaluation

The proposed primary endpoint and methods for the economic evaluation follow the reference case set out by the National Institute for Health and Care Excellence (NICE) [80]. The primary economic analysis will be a cost-utility analysis over 16 months presenting incremental cost-effectiveness ratios (ICER) for intervention (UC + DCM™) versus control (UC), with effects expressed in terms of quality-adjusted life years (QALY). The analysis will adopt the health care and personal social services perspective. Analysis of the uncertainty surrounding the ICER will be undertaken using non-parametric bootstrap simulation (10,000 simulations) and presented on a cost-effectiveness plane and a Cost-Effectiveness Acceptability Curve (CEAC) [81]. A net benefit regression approach will also be employed using the model selected for the clinical effectiveness analysis [82]. Where Net Monetary Benefit (NMB) = (£20,000 × QALYs) − Costs NMB regression will enable covariate control and clustered analysis. There will be no modelling forward of benefits and discounting (at 3.5 %) will be conducted for values post 12 months. We will use the NICE willingness to pay per incremental QALY threshold range (lambda [λ] = £20,000-£30,000) to determine cost-effectiveness.

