## Methods/design

### Design

This trial has been designed to be a pragmatic, multi-centre, cluster-randomised controlled trial of DCM™ plus UC versus UC alone. There will be four types of trial participants: care homes, residents, their relative/friend and care home staff members. The trial will take place in residential, nursing and dementia UK care homes across West Yorkshire, Oxfordshire and London. From these areas, 50 care homes will be recruited from a random sample, within which 750 residents, their relative/friend (where eligible) and all eligible, consented, care home staff will be registered. Following participant identification and consent, baseline assessments will be undertaken and then the care homes will be randomised in a ratio of 3:2 to receive intervention or control. Outcome measures will be obtained at 6 and 16 months following randomisation. Additional to the primary analysis, there will be an integral cost-effectiveness analysis and a process evaluation. Figure 1 outlines the schedule for all trial activities.

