### Data assessments

Assessments will be undertaken at screening (prior to consent); baseline (prior to resident registration); 6 months post randomisation and 16 months post randomisation. Baseline data collection visits will be conducted over approximately 3 weeks in each home and follow-up visits over a 1–2-week period. Required data, assessment tools, collection time points and processes are summarised in Table 1.

**Table 1 Tab1:** Summary of assessments

Assessment	Type	Method of completion	Timeline			
			Screening	Baseline	6 months	16 months
Care home eligibility	CRF	Researcher assessment	X			
Training review	CRF	Researcher assessment	X			
Dementia awareness training	CRF	Dementia awareness trainer	X			
Resident screening (demographics)	CRF	Researcher assessment	X			
Staff mapper screening	CRF	Researcher assessment	X			
Consent (staff mapper, resident (includes personal/nominated consultee), staff proxy informant, RF proxy informant)	Consent Form	Self-completion (witnessed)	X			X
Participant eligibility (staff mapper, resident, staff proxy informant, RF proxy informant)	CRF	Researcher assessment	X			X
Participant contact details (resident, staff proxy informant, RF proxy informant)	CRF	Researcher assessment	X			X
Cohen-Mansfield Agitation Index (CMAI) abridged	Questionnaire booklet	Independent researcher observations (R)		X	X	X
Pittsburgh Agitation Scale (PAS)	Questionnaire booklet	Independent researcher observations (R)		X	X	X
Care home manager demographics	Questionnaire booklet	Researcher interview (CM)		X	X	X
Care home demographics	Questionnaire booklet	Researcher interview (CM)		X	X	X
Group Living Home Characteristics (GLHC)	Questionnaire booklet	Researcher assessment (CH)		X	X	X
Environmental Audit Tool (EAT)	Questionnaire booklet	Researcher observations (CH)		X	X	X
Quality of Interactions Schedule (QUIS)	Questionnaire booklet	Researcher observations (R/S)		X	X	X
Staff proxy informant demographics	Questionnaire booklet	Researcher interview (SP)		X	X	X
Resident demographics	Questionnaire booklet	Researcher assessment		X	X	X
RF proxy informant demographics	Questionnaire booklet	Researcher interview (RF)		X	X	X
Cohen-Mansfield Agitation Index (CMAI)	Questionnaire booklet	Researcher interview (SP)		X	X	X
Neuropsychiatric Inventory (NPI-NH)	Questionnaire booklet	Researcher interview (SP)		X	X	X
Functional Assessment Staging (FAST)	Questionnaire booklet	Researcher interview (SP)		X	X	X

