#### Effects

Utility values will be captured using the EQ-5D-5 L (primary) and DEMQOL-Proxy-U [83] (secondary). Residents will self-report where able on the EQ-5D-5 L or the EQ-5D-Proxy will be used. Resident- and proxy-reported data will be reported and analysed separately. However, given that only a proportion of residents will be able to complete the questionnaires, we will explore whether it is valid to use one source of data as a substitute for the other.

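### The net-benefit regression borrows the agitation model, whose listed covariates include baseline CMAI but not baseline utility, so a chance utility imbalance would carry into the economic result

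*Protocol article*

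**What the plan says.** Under Health economic evaluation, "The primary economic analysis will be a cost-utility analysis over 16 months", "with effects expressed in terms of quality-adjusted life years (QALY". Uncertainty around the ICER is handled by a non-parametric bootstrap, for which no covariate adjustment is mentioned. The text then adds: "A net benefit regression approach will also be employed using the model selected for the clinical effectiveness analysis", and gives the reason that "NMB regression will enable covariate control and clustered analysis". It does not name the covariates.

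The only clinical model with a covariate list is the primary CMAI model under Statistical analysis. It has four home-level covariates (type, size, dementia awareness training, hub) and "resident (level 1) covariates (severity of dementia, age and baseline CMAI score". Baseline utility is not named as a covariate anywhere in the article.

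Under Effects, "Utility values will be captured using the EQ-5D-5 L (primary) and DEMQOL-Proxy-U [83] (secondary"). Assessments after screening take place at "baseline (prior to resident registration); 6 months post randomisation and 16 months post randomisation" (Data assessments), and Table 1 marks the EQ-5D-5L, DEMQOL-Proxy and health care resource use at all three. The Design section fixes the order: "baseline assessments will be undertaken and then the care homes will be randomised in a ratio of 3:2". The article does not say how QALYs are computed from these measurements.

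**The concern.** The clinical model adjusts the CMAI for its own baseline. Carried over with its listed covariates, it adjusts net benefit for the baseline of a different outcome and not for its own. Baseline utility matters here in two ways. It would normally be one of the points from which the QALY is built, because the first six months have no other starting value. It also predicts the 6- and 16-month utilities.

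If the arms happen to differ in utility before randomisation, the unadjusted part of that difference is read as QALYs gained or lost. The minimisation factors are all care home characteristics and none measures utility, so nothing in the allocation guards against this directly. Cost-effectiveness is the second limb of the primary objective, so both the point estimate and its precision matter.

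**Working it through.** The article gives no figure for the QALY or net-benefit analysis, so there is none to reproduce. Its CMAI power statement does not bear on this point.

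**Inputs from the article.** Utility at 0, 6 and 16 months; 50 homes of 15 residents, 3:2, hence 30 × 15 = 450 against 20 × 15 = 300 residents; £20,000 per QALY, the lower end of the stated threshold range.

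**Assumptions not in the article.** QALYs by linear interpolation between visits; utility SD 0.25 (range 0.20 to 0.30); utility ICC 0.1 (range 0.05 to 0.10; the article's 0.1 is an upper limit for the CMAI); persistence ρ of baseline into follow-up utility between 0 and 0.8.

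**Step 1, weight of baseline.** The intervals are 0.5 and 0.833 year.

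QALY = 0.5 × (u0 + u6)/2 + 0.833 × (u6 + u16)/2 = 0.25 u0 + 0.667 u6 + 0.417 u16.

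The weights sum to 1.333 years, and baseline has 0.25/1.333 = 18.75%.

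**Step 2, likely size of a chance imbalance.** Design effect = 1 + 14 × 0.1 = 2.4.

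SE = 0.25 × √(2.4 × (1/450 + 1/300)) = 0.029.

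Over the ranges of SD and ICC above, the SE runs from 0.019 to 0.035.

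**Step 3, effect on net benefit with no covariates.** Shift in incremental QALYs = imbalance × (0.25 + 1.083ρ), where 1.083 = 0.667 + 0.417 before rounding. For a one-SE imbalance:

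| ρ | Multiplier | QALY shift | At £20,000 per QALY |
|---|---|---|---|
| 0 | 0.250 | 0.007 | £144 |
| 0.5 | 0.792 | 0.023 | £457 |
| 0.8 | 1.117 | 0.032 | £645 |

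**Step 4, how much baseline CMAI removes.** Step 3 does not describe the planned model, which has covariates. A simulation with no treatment effect used 50 homes of 11 analysed residents, 3:2, ICC 0.1, SD 0.25 and ρ = 0.5. It compared adjustment for baseline CMAI alone with the same model plus baseline utility, by ordinary least squares. Results are for the QALY part of net benefit at £20,000 per QALY. Without covariates, a 0.05 imbalance would shift net benefit by 0.05 × 0.792 × £20,000 = £792.

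| Assumed CMAI–utility correlation | Shift per 0.05, CMAI only | Shift per 0.05, plus baseline utility | SD of estimate, CMAI only | SD of estimate, plus baseline utility |
|---|---|---|---|---|
| −0.1 | £800 | £13 | £641 | £416 |
| −0.3 | £730 | £12 | £631 | £424 |
| −0.5 | £596 | £7 | £605 | £417 |

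CMAI alone removes at most about a quarter of the shift (596/792 = 0.75). Adding baseline utility removes essentially all of it and cuts the variance of the QALY part by roughly half: (416/641)² = 0.42 and (417/605)² = 0.47. The mean error with CMAI only was between −£44 and £8, small against an SD above £600. Its expectation is zero by construction, since arm is unrelated to baseline. Dementia severity, age and the home-level factors were not simulated and would absorb some more.

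**The case against.** The strongest objection is that this is a condensed article. The full protocol and the analysis plan are not shown, and a covariate list or QALY rule may properly sit there. The reference to the selected model can also be read as model form: the two-level heteroscedastic structure rather than the equal-variance alternative. The text says covariates will be controlled without naming them, and secondary outcomes get a similar strategy, which most analysts would take to mean each outcome with its own baseline. This stands as a reason for restraint, since the article does not explicitly exclude baseline utility. It does not dispose of the point. The economic model is set by cross-reference, and the only list at the other end was written for the CMAI.

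Three stronger readings are tempting and are not supported:

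- **That the economic result will be biased.** Baseline is collected before homes are randomised, so any imbalance is due to chance. The cost is error conditional on the imbalance that occurs, plus lost precision.
- **That the whole imbalance is counted as QALYs, or that the QALY is stated to be an area under the curve.** The planned covariates absorb part of the imbalance. The area-under-the-curve construction is a strong inference from the visit schedule, not stated text.
- **That the shift rivals a plausible QALY gain or would reverse the decision.** The article gives no expected QALY gain or cost difference to compare it with.

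The net-benefit regression is also additional to the cost-utility analysis that is labelled primary. That limits the weight of the quoted sentence, but no adjustment is stated for the ICER either.

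**Conclusion.** The point holds in a limited form. Taken literally, the article adjusts net benefit for baseline CMAI and not for baseline utility, and states no adjustment for the ICER. Under the usual QALY construction, baseline utility has about 19% of the weight, and a chance arm difference in it would pass largely into the economic estimate.

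The pound figures are illustrations. They rest on an assumed utility SD, ICC and persistence, and the £144 to £645 range is before any covariate adjustment, so the planned model would show less. The direction does not depend on those values: whenever baseline utility predicts later utility, leaving it out costs precision and leaves part of a chance imbalance in the result. This is a worthwhile improvement to the specification, not an error that invalidates the economic analysis.

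**What to change.** In Health economic evaluation, state that the net-benefit regression, and the incremental QALYs behind the ICER, keep the clinical model's clustering structure and home-level covariates. State that baseline CMAI is replaced or supplemented by the baseline value of the same utility measure, from the same informant, that forms the QALY. Say in the same place how QALYs are computed from the three visits. Baseline health care cost may be added for the cost component; this is optional, and no calculation here rests on it.

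The cost is a sentence or two of text. No new data are needed: the EQ-5D-5L, DEMQOL-Proxy and resource use are already in the baseline schedule. If the full protocol or analysis plan already specifies this, a cross-reference is enough.

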#### Effects

Utility values will be captured using the EQ-5D-5 L (primary) and DEMQOL-Proxy-U [83] (secondary). Residents will self-report where able on the EQ-5D-5 L or the EQ-5D-Proxy will be used. Resident- and proxy-reported data will be reported and analysed separately. However, given that only a proportion of residents will be able to complete the questionnaires, we will explore whether it is valid to use one source of data as a substitute for the other.

#### Costs

The total cost of DCM™ will incorporate the costs of training staff and staff time spent delivering the intervention as well as travel costs and any other expenditure (e.g. on training materials). The assumption for the analysis will be that the local authority pays for the provision of care home care for residents. We will include a sensitivity analysis where a proportion of residents are considered to pay toward their care home costs. Researchers will collect health care resource use data for each resident participating in the trial at baseline, 6 and 16 months using individual care home records and care plans. This will be supplemented by care home-level data collection, which will enable some validation of individual-level data. Unit costs for health service staff and resources will be obtained from national sources such as the Personal Social Services Research Unit, the *British National Formulary* and NHS reference cost database.

### Trial governance

The Trial Management Group, comprising the chief investigator, CTRU team, co-investigators and researchers will be assigned responsibility for the clinical set-up, on-going management, promotion of the trial, and for the interpretation of results. An independent Data Monitoring and Ethics Committee will be established to review the safety and ethics of the trial. An independent Trial Steering Committee will be established to provide overall supervision of the trial, including trial progress, adherence to protocol, resident safety, and consideration of new information. The trial sponsor will ensure responsibility and accountability for trial conduct and procedures associated with the protocol. Individual care homes remain responsible for participant care as usual. Trial researchers will have the opportunity to highlight any safeguarding issues of concern with the Trial Steering Committee and to individual care homes, in line with relevant guidance from the local authority, care home, and the trial team.

### Public and Patient Involvement

Service users and carers will play an integral role throughout this programme of research to ensure that the work is based on the principles of Patient and Public Involvement (PPI). PPI will be fulfilled in partnership with the Alzheimer’s Society via involvement of members of their Research Network, and via inclusion of PPI representatives (relatives and persons with Dementia) on the Trial Management Group and Trial Steering Committee. Specifically, PPI representatives will be involved in the review of participant information and general aspects of trial design and be involved in all decisions made by the Trial Management Group. The intention is to involve service users in the interpretation of results and appropriate dissemination of information at the end of the trial.

## Discussion

### Pilot phase

A pilot was built into the trial to pilot trial procedures to inform modification to, and streamlining of, research processes for the remaining care homes. Two care homes (one in West Yorkshire, one in London), were recruited to the pilot 2 months ahead of start of the planned recruitment phase. Three review periods followed: the first focussed on care home screening and recruitment processes, the second assessed trial burden to participants, and the third adherence to determine if data collection needed to be adapted or reduced. The trial procedures described above were followed, and experiences reviewed by the trial team. The changes made are summarised below. Pilot homes will be included in the final analysis.

#### Screening and recruitment review

One change made as a result of this review was improvement to the Case Report Forms (CRFs). Changes to the content and structure of some CRFs and creation of new forms ensured that all CRFs reflected actual processes and procedures that the researchers needed to follow to accurately complete the complex screening and recruitment process. A second change was made to care home eligibility criteria. Originally, the criteria stated that to be eligible a care home should have a minimum of 24 permanent residents of whom at least 60 % were estimated to have dementia. However, this did not always ensure that recruited care homes would be able to provide an adequate number of trial participants. For example, large residential homes where the general resident population did not include many people with dementia, but contained a smaller specialist dementia unit failed to reach the threshold of 60 % of residents with dementia within the care home overall but could still achieve a viable cluster size of residents with dementia within the specialist unit. Likewise, in smaller homes, an adequate cluster of eligible residents was not always available when both the 24 permanent residents and the ‘60 % of residents with dementia’ criteria were met, due to eligibility exclusions based on other, resident-level, criteria. This was particularly the case for nursing homes where residents had a range of significant additional physical health problems. On the other hand, the criteria also led to the exclusion of some smaller dementia-specialist care homes that would have been able to provide an adequate cluster size despite having less than 24 permanent residents in total. As a result, care home eligibility criteria were replaced with the following:

• Has a sufficient number of permanent residents with dementia (based on a formal diagnosis or Functional Assessment Staging of Alzheimer’s Disease (FAST) score of 4+) eligible to participate in the study in order to achieve a minimum of 10 residents registered to take part prior to care home randomisation

